**Protocol ID NL42367.018.12****Reflux symptoms in achalasia**

pH 7 and pH 1. The catheter will be positioned in such a way that the pH sensor is located 5 cm above the LES, which is based on manometry readings.

*Analysis of the data of the HRM and pH-impedance monitoring*

For analysis of the data obtained with HRM and pH-impedance measurement MMS software (Enschede, The Netherlands) will be used. Observers will be blinded for patient characteristics when analyzing the measurement.

The HRM will give insight in the esophageal function. It provides information on the contractile activity of the esophageal body and the esophagogastric junction including the LES. Therefore it is helpful in distinguishing transient LES relaxation (TLESRs), which occurs in GERD, from pseudorelaxation of the LES by shortening of the esophageal body. pH-impedance monitoring provides information on esophageal bolus transit. Combined with HRM it can distinguish GER from retention and fermentation of food. GER is characterized by TLESRs and a retrograde moving decrease in impedance with an abrupt drop in pH levels followed by normalisation of the impedance and pH. In case of fermentation there is a slow and longer decrease in impedance and pH. The pH-impedance monitoring will also record all reflux episodes, both acid as non-acid, during the 24-hours measurement. During the analysis of the data of the pH-impedance monitoring reflux symptoms will be correlated with acid and non-acid reflux episodes. A positive correlation is declared if a specific reflux symptom is preceded by a reflux episode within two minutes.

*Acid perfusion test*

Patients will undergo an acid perfusion test, according to a previously described protocol. The manometry catheter used for the HRM (Unisensor AG, Attikon Switzerland) will be placed in the esophagus in such a way that the additional side-hole is placed at 5 cm above the LES. After an adaption period of 10 minutes saline will be infused in the distal esophagus for 10 min, followed by hydrochloric acid (0.1N) for 30 min or until the study subject experiences pain. Both saline and hydrochloric acid will be instilled at a rate of 8 mL/min, controlled by an automatic pump (IVAC 560 Volumetric Pump; Rhys Int. Ltd, Bolton, UK). Study subjects will be blinded to the nature of the infusate and will be asked to report the first sensation of heartburn, discomfort and pain. When study subjects experience pain, acid infusion will be discontinued immediately. After every elapsed minute during the acid perfusion test, patients will be asked whether their sensation changes. The time from start of acid infusion (marked by a pH drop to pH < 1.0), necessary to provoke first perception, discomfort and pain will be noted and represents a measure of sensitivity.

**Protocol ID NL42367.018.12****Reflux symptoms in achalasia***Timed barium esophagram*

A maximal tolerable amount of low density barium sulphate has to be ingested by the study subjects in 30-45 s without regurgitation or aspiration. After ingestion of low density barium sulphate esophageal stasis will be determined at 1, 2 and 5 minutes with the study subject upright in a slight left posterior position. The distance from the tapered distal esophagus to the top of the barium column and the maximal diameter of the esophagus are measured.

*Questionnaires*

- Eckardt score, which is the sum of symptom scores for dysphagia, regurgitation, chest pain and weight loss. Each symptom is scored from 0 to 3. The minimum score is 0 and the maximum score is 12.
- The validated Achalasia Disease-Specific Quality-of-Life questionnaire (Achalasia-DSQoL).
- The validated Gastroesophageal Reflux Disease Questionnaire (GERDQ) is a self-assessment questionnaire that can be used to for the diagnosis and follow-up of gastroesophageal reflux disease. It measures both symptoms and impact of symptoms on person's daily life.
- Medical Outcomes Study 36-Item Short-Form Health Survey (SF-36). The SF-36 mental and physical summary scores (range from 0-100 and higher scores indicate better well-being) measure general aspects of health quality of life.

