Study subjects will arrive in the morning at the clinic after an overnight fast, no intake of fluid after midnight except water. Preferably the intake of medication should be postponed after the measurements. If this is not possible medication should of course be ingested prior to the measurements. Before the first measurements patients must have been fasting for two hours, so also no intake of water. The catheter for the Endoflip will be placed transnasally. After this measurement the catheters for the esophageal HRM and pH-impedance will be placed transnasally. Before placement of the pH-impedance catheter, an acid perfusion test will be performed using the HRM catheter. The combined HRM and pH-impedance measurement will be performed in the fasting condition for half an hour followed by a postprandial measurement of 3.5 hours after a standardized liquid meal, 400 mL nutrient drink (600 kcal Nutridrink, Nutricia, the Netherlands) with 200 mL water. The liquid meal will be administered by the catheter used for the HRM. After this the HRM catheter will be removed while the pH-impedance catheter will stay in place and reflux will be monitored for the next 20 hours. The standard investigation for patients with reflux symptoms is 24-hour pH-impedance monitoring. Study subjects go home with the pH-impedance catheter in place and will receive a diary to write down there symptoms. During this measurement the study subject has to drink and eat at regular moments but there is no restriction concerning the food intake, except again an overnight fast due the timed barium esophagography the next day. The following day patients come back to the clinic where the pH-impedance catheter will be removed and a timed barium esophagography will be performed, which is the last measurement.

**5.2.2 Procedures and questionnaires***Endo Functional Luminal Imaging Probe (EndoFLIP)*

To determine the distensibility of the esophagogastric junction (EGJ) and the esophagus the EndoFLIP system will be used (MMS, Enschede, the Netherlands). The measurement with the EndoFLIP will be performed according to a previously described protocol. A probe is

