**Protocol ID NL42367.018.12****Reflux symptoms in achalasia**

inserted into the esophagus and placed at the level of the EGJ. The probe consists of a 240-cm catheter with a 14-cm bag attached to its distal end, which is compliant to a maximal diameter of 25 mm. Inside the bag 17 electrodes are placed at 4-mm intervals. An excitation current of 100µA is generated between two adjacent electrodes at a frequency of 5 kHz. Using impedance-planimetry cross sectional areas (CSAs) are determined for the 16 balloon cross sections during volume controlled distensions. Additionally two pressure sensors are located on the probe to determine intrabag pressure allowing assessment of EGJ distensibility.

The distension probe and the pressure transducers are calibrated by the manufacturer. The pressure sensor is zeroed prior to transnasally insertion of the catheter. Previous manometry readings of the study subjects will be used to position the balloon at the EGJ. The balloon will be inflated to a 20, 30, 40, 50, 60 and 70 mL volume. Pressures and CSAs are collected at a rate of 10 Hz. Distensibility is assessed using the median value over a 30 s dynamic measurement of the narrowest CSA, which corresponds to the EGJ, and the median intrabag pressure.

After measuring the EGJ distensibility the catheter will be placed 10 cm above the LES and the balloon will be inflated to a 20, 30, 40, 50, 60 and 70 mL volume. The time between each inflation will be 30 seconds and study subjects will be asked after each inflation whether they experience pain or other symptoms.

*High Resolution Manometry (HRM)*

A water-perfused high-resolution manometry assembly with 21 water-perfused sensors spaced at 1-cm intervals at the position of the esophagogastric junction will be used (Medical Measurement Systems, Enschede, The Netherlands). Each sensor is accurate to within 1 mmHg, capable of recording transient pressure changes in excess of 6000 mmHg/s, and zeroed to atmospheric pressure. The high-resolution manometry assembly will be introduced transnasally and positioned to record from hypopharynx to stomach with about five intragastric sensors. Data are analyzed using Solar high-resolution manometry software (Medical Measurement Systems, Enschede, The Netherlands).

*pH- impedance monitoring*

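### Reader blinding is stated only for manometry and pH-impedance, not for the barium readings, and the pH-impedance analysis sets no order between scoring episodes and seeing the symptoms

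*Protocol*

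**What the plan says.** **Where blinding is stated.** Section 5.2.2 of the protocol, under the analysis of HRM and pH-impedance data, opens with "For analysis of the data obtained with HRM and pH-impedance measurement MMS software (Enschede, The Netherlands) will be used" and continues with "Observers will be blinded for patient characteristics when analyzing the measurement". The only other blinding is in the acid perfusion test, and it concerns the patients: "Study subjects will be blinded to the nature of the infusate".

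**Where it is not stated.** The timed barium text says "The distance from the tapered distal esophagus to the top of the barium column and the maximal diameter of the esophagus are measured". The EndoFLIP text says "Distensibility is assessed using the median value over a 30 s dynamic measurement of the narrowest CSA", together with the median intrabag pressure. Neither says who reads the record or what that reader knows.

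**Group and expected direction.** Sections 4.2.1 and 4.2.2 define the groups by reflux symptoms and a GERDQ score of at least 8 or below 8. Under section 5.2.1 the GERDQ is completed before any measurement, to confirm the group. Section 4.4 names LES pressure, EGJ distensibility and stasis as the main secondary parameters. It expects lower distensibility and more stasis in the symptomatic group.

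**Symptoms in the pH-impedance analysis.** Section 5.2.1 states "Study subjects go home with the pH-impedance catheter in place and will receive a diary to write down there symptoms". Section 5.2.2 states "During the analysis of the data of the pH-impedance monitoring reflux symptoms will be correlated with acid and non-acid reflux episodes", using a two-minute window.

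**The concern.** The study compares two groups defined by symptoms, and the investigators have said which way they expect the results to go. A reader who knows the group can move a borderline measurement in that direction without intending to. Such an error differs between the groups, so it does not average out. It adds to the group difference, and no later analysis can remove it from the recorded values.

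Two separate places are open to this:

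- **Barium stasis and width.** Both are manual distances with no stated reader blinding. EndoFLIP distensibility has the same gap but leaves less to the reader.
- **Reflux episodes.** Blinding to patient characteristics is promised, but the symptoms are used in the same analysis. Having or not having those symptoms is what defines the group. A scorer who sees the symptom entries while marking episodes may in effect know the group.

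**Working it through.** **1. Coverage of the blinding sentence, by outcome in section 5.1**

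| Outcome | Source | Reader blinding stated? | Room for reader judgement |
|---|---|---|---|
| Reflux episodes (primary) | pH-impedance with HRM | Yes, but symptoms enter the same analysis | Identifying an episode; GER versus fermentation by trace shape |
| LES pressure (main secondary) | HRM | Yes | Not at issue |
| EGJ distensibility (main secondary) | EndoFLIP | No | Small: median of recorded signals at fixed volumes |
| Stasis (main secondary) | Timed barium | No | Manual distance |
| Esophageal width | Timed barium | No | Manual diameter |

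So two of the three main secondary parameters, plus width, lie outside the sentence. Sensitivity to acid and distension is reported by the patient and is not a reader measurement.

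**2. The protocol's own stasis figure**

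Inputs from section 4.4: difference 1.2 cm, SD 1.2 cm, two-sided 5%, power 80%, two-group t-test. The noncentrality is (difference / SD) × √(n/2). With n = 17 this is 1.0 × √8.5 = 2.92 on 32 degrees of freedom, and the power is 80.7%. Solving for 80% gives n = 16.7, hence 17 per group as stated. The figure reproduces and is not disputed.

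**3. What a reading shift would do to stasis (illustration)**

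Take the planned 20 per group, SD 1.2 cm and no true difference. Add a systematic shift b to one group's readings. The noncentrality is (b / 1.2) × √(20/2) = (b / 1.2) × 3.162, on 38 degrees of freedom.

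| Assumed shift b | Noncentrality | Chance of a significant result |
|---|---|---|
| 0 | 0 | 5% |
| 0.25 cm | 0.66 | 9.8% |
| 0.5 cm | 1.32 | 25.0% |

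The SD and group size are the protocol's. The shifts are assumptions. They equal 0.25/1.2 = 21% and 0.5/1.2 = 42% of the planned difference.

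**4. The primary contrast**

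Section 4.4 powers 30% versus 75% of patients with reflux episodes caused by GER or by fermentation, counted together. Relabelling an episode from one cause to the other leaves the patient positive, so the pooled contrast does not change. Two things can change if the scorer knows the group: whether a doubtful event is counted as an episode at all, and the split between GER and fermentation. That split bears on the hypothesis in section 2. Section 5.2.2 separates the two by whether the fall is abrupt or slow and longer, without a numeric threshold.

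**The case against.** **Silence is not unblinded reading.** The protocol does not say that the barium or EndoFLIP records are read with knowledge of the group. The staff who check the GERDQ need not be the readers. This stands: a reader might infer that these records are read unblinded, and the document does not show that. It shows only that nothing prevents it.

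**Data are already coded.** Sections 7 and 10.1 require study numbers in order of participation, and such a number does not itself reveal the group. This makes the remedy cheaper. But the coding serves privacy and the investigators can open it, so it does not mask readers.

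**EndoFLIP is not comparable to barium.** Volumes are fixed, signals are recorded at 10 Hz and a median is taken. This stands. Most of the remaining judgement is balloon placement at the bedside, which blinded re-reading would not correct.

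**The primary observers are blinded, and the symptom link follows a fixed rule.** Both are true. The text does not say that the scorer sees the diary while scoring, so unmasking is an inference. The missing element is the order of the steps.

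**The shifts have no source.** Correct. They show what a bias of that size would do, not that it is likely.

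**Conclusion.** The point holds in a limited form. Reader blinding is not stated for barium stasis and width, which are manual readings made after the group is confirmed and with a stated expectation. EndoFLIP shares the gap to a lesser degree. As a separate matter, the order of episode scoring and symptom linkage is left open, which could weaken the blinding promised for pH-impedance.

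Two stronger readings are tempting and not supported. One is that the diary explains the barium and EndoFLIP gap. It has no part in it; that gap comes from the narrow scope of the blinding sentence. The other is that confusing GER with fermentation undermines the powered primary comparison. It does not, because that comparison pools both causes.

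The size cannot be estimated from the document. Under the assumed stasis shifts of 0.25 and 0.5 cm, the false-positive rate would be about 10% and 25% instead of 5%. This rests on the protocol's SD of 1.2 cm, 20 per group, and a uniform shift across one group. No size is claimed for the primary parameter. The information given to readers is a matter of study conduct, so a later analysis plan could not repair readings already made. The change is worth making because it is cheap; no sample size is affected.

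**What to change.** 1. Extend the blinding sentence in section 5.2.2 to the timed barium films, and also to the EndoFLIP recordings. Have them read as coded files, without group, questionnaire or symptom data, by the observers who are already blinded for HRM and pH-impedance.
2. For pH-impedance, state the order: identify and classify all episodes with symptom marks hidden, lock that record, then add the diary and apply the two-minute rule.

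The cost is a short change of wording, preparation of masked files and reading in two steps. There is no extra procedure for patients, and the coding already required can be used, provided the readers have no access to the key.

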**5.2.1 Research protocol**

**Protocol ID NL42367.018.12****Reflux symptoms in achalasia**

Baseline clinical data will be collected using different questionnaires. Before any measurement will be performed the participant will be subjected to the GERD Questionnaire to be certain that he or she is allocated in the correct study group.

For this study all included study subjects will undergo five different measurements in two following days, as outlined in the schematic overview. The first measurement will be performed with impedance planimetry, using the Endo Functional Luminal Imaging Probe (EndoFLIP). The Endoflip can determine the esophagogastric junction distensibility and examine the esophageal distensibility. The measurement with the Endoflip will be followed by an acid perfusion test, the Bernstein test. The perfused catheter used for the high-resolution manometry will be used to infuse the acid and control solutions. The acid perfusion test will provide information about the sensitivity for acid in the esophagus. After the acid perfusion test a combined measurement of high-resolution manometry (HRM) and pH-impedance monitoring will be carried out. The catheter used for the acid perfusion test is the same as the catheter for the HRM. After 3-4 hours the HRM catheter will be removed and the pH-impedance catheter will remain in place for a further 24-hour measurement of reflux episodes and symptoms. After 24-hour pH-impedance monitoring the catheter will be removed and a timed barium esophagography will be performed. The barium esophagography is performed to gain insight into esophageal emptying and the width of the esophagus.

**Schematic view of the study design**[figure not shown]

**Protocol ID NL42367.018.12****Reflux symptoms in achalasia***Study requirements and timeline*

The measurements will be performed after cessation of PPIs, H2-antagonists and medications which can influence intestinal motility for 1 week. A temporary stop of PPI, H2-antagonist or prokinetic drug prior to reflux monitoring is not harmful for the patient and is in concordance with the reflux guideline of the Dutch association of gastroenterologists. For the reduction of severe symptoms patients are allowed to take rescue medication in the form of antacids. Furthermore, one day before the measurements the patients will be restricted to a liquid diet to minimise stasis of food in the esophagus.

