A pH-impedance catheter will be introduced transnasally. A 2.1-mm outer diameter study catheter comprised of six electrode pairs measuring intraluminal impedance at 3, 5, 7, 9, 15 and 17 cm above the LES and an ISFET pH sensor, placed 5 cm above the LES will be used. Before and after recording the pH electrode will be calibrated using standard buffers of

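### The acid-sensitivity clock is marked by a pH below 1.0, which 0.1N HCl cannot produce and no pH sensor described as in place could record; the handling of residual acid before the primary recording is also unstated

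*Protocol*

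**What the plan says.** Sensitivity to acid perfusion is a listed secondary parameter (Protocol section 5.1.2). Section 5.2.2 (Acid perfusion test) describes its measurement. The control step comes first, after an adaptation period: "saline will be infused in the distal esophagus for 10 min". The text then gives the acid step and its stopping point: "followed by hydrochloric acid (0.1N) for 30 min or until the study subject experiences pain". On the rate: "Both saline and hydrochloric acid will be instilled at a rate of 8 mL/min", controlled by an automatic pump. The outcome is "The time from start of acid infusion (marked by a pH drop to pH < 1.0") to first perception, discomfort and pain.

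On the order of procedures, section 5.2.1 says: "Before placement of the pH-impedance catheter, an acid perfusion test will be performed using the HRM catheter". It also says: "After the acid perfusion test a combined measurement of high-resolution manometry (HRM) and pH-impedance monitoring will be carried out". That combined recording opens with a fasting half-hour and continues for 3.5 hours after a standardized liquid meal. The pH-impedance catheter then stays in for a further 20 hours.

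On equipment, section 5.2.2 describes the manometry catheter as "A water-perfused high-resolution manometry assembly with 21 water-perfused sensors spaced at 1-cm intervals", and mentions no pH electrode on it. The pH-impedance catheter carries "an ISFET pH sensor, placed 5 cm above the LES will be used", calibrated in buffers of pH 7 and pH 1.

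The primary parameter is gastroesophageal reflux episodes (section 5.1.1), which the 24-hour pH-impedance recording supplies.

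**The concern.** The event that starts the clock has to be one that the infusate can cause and the equipment can register. As written, it appears to be neither. If the marker cannot be used, each operator has to choose a substitute, such as pump start, arrival of acid at the side-hole or first reported change. The times are then not defined in the same way for all subjects.

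The second concern is sequence. The protocol prescribes a liquid diet the day before to limit stasis, and its hypothesis rests on reduced clearance from aperistalsis (section 2). It then infuses saline and acid into the distal esophagus shortly before the recording that yields the primary parameter. It states no interval, baseline check or excluded period. The amount infused depends on the subject's response, because infusion stops at pain, and section 2 expects acid sensitivity to differ between the groups. Any residual effect could therefore differ between groups.

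**Working it through.** **1. Can the infusate reach the marker?**

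Inputs: acid concentration 0.1 mol/L (0.1N, monoprotic, fully dissociated) and threshold pH < 1.0, both from section 5.2.2. The activity coefficient *g* and the acid fraction *f* after dilution are not in the protocol. They are assumptions, shown as ranges.

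Formula: pH = -log10(0.1 × *g* × *f*).

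| Case | *g* | *f* | pH |
|---|---|---|---|
| Most favourable to the protocol | 1.00 | 1.00 | 1.00 |
| Activity only | 0.85 | 1.00 | 1.07 |
| Activity only | 0.80 | 1.00 | 1.10 |
| Activity only | 0.75 | 1.00 | 1.12 |
| Dilution only | 1.00 | 0.90 | 1.05 |
| Dilution only | 1.00 | 0.75 | 1.12 |
| Dilution only | 1.00 | 0.50 | 1.30 |

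The Davies equation gives *g* of about 0.78, hence a pH of about 1.11. No case falls below 1.0, and the best case only equals it. Some dilution is expected, because 10 min × 8 mL/min = 80 mL of saline has just been infused at the same site. A displayed value under 1.0 could come only from sensor error, and it would lie outside the pH 1 to pH 7 calibration span.

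**2. Is there a sensor to see it?**

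- Acid test: performed through the manometry catheter, described with water-perfused pressure sensors (sections 5.2.1 and 5.2.2).
- pH sensor: described only on the pH-impedance catheter (section 5.2.2).
- Placement of that catheter: after the acid test (section 5.2.1).

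Read together, no pH sensor is described as being in place during the test.

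**3. What time zero is available instead?**

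The pump switch from saline to acid is observable. The delay until acid leaves the side-hole is dead volume ÷ 8 mL/min, so each 8 mL of dead volume adds one minute. The dead volume is not stated. Sensation is queried every minute, so a dead volume under 8 mL gives a delay shorter than the query interval.

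**4. How much acid precedes the primary recording?**

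- Maximum acid volume: 30 min × 8 mL/min = 240 mL, which is 240 mL × 0.1 mmol/mL = 24 mmol. It is less if infusion stops for pain.
- Bringing 0.1N acid to pH 4 without buffering needs a dilution of 0.1 ÷ 0.0001 = 1000-fold.
- Recording length: 0.5 + 3.5 + 20 = 24 h = 1440 min. The fasting half-hour is 30 ÷ 1440 = 2.1% of it.

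These figures show what is infused, not what remains when recording begins. The protocol gives nothing from which the remainder could be calculated.

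**5. Which way would carry-over act?**

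If symptomatic patients are the more acid-sensitive, they stop earlier and receive less acid. Section 4.4, however, expects lower junction distensibility and more stasis in that group, which would hold acid longer. The two effects oppose each other, so the net direction is open.

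**The case against.** The interval is defined from the start of acid infusion, and the pH drop is only a parenthetical marker of that event. The pump makes the event visible, and a line delay common to all subjects matters little to a comparison between groups. This stands. A reader might infer that time zero does not exist for any patient. The text does not support that, because the defect lies in the written marker.

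The equipment description may be incomplete. The test follows a cited procedure, and it uses a side-hole that the manometry paragraph does not mention. Section 5.2.1 also first speaks of both catheters being placed after the EndoFLIP, before putting the acid test ahead of the second. This partly stands: one can say that no pH sensor is described as in place, not that none could be. It does not rescue the threshold, which fails on arithmetic alone.

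On carry-over the objection is stronger. Section 5.2.2 characterises fermentation by a slow, prolonged fall in impedance and pH, whereas acid that is clearing gives a rising pH. Reflux is characterised by sphincter relaxation and a retrograde impedance drop, which static acid does not produce. Placing the second catheter takes time, and a meal with water follows the fasting half-hour. Scoring rules and excluded windows may also sit in an analysis plan. What remains is that the protocol itself fixes the order and says nothing about a recording that begins at low pH.

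**Conclusion.** The written marker for the start of acid infusion is wrong. The stated infusate cannot produce it under any assumption tried (pH 1.00 at best, about 1.05 to 1.30 with activity or dilution allowed for), it lies below the calibration range, and the described catheter order leaves no sensor to register it. This affects the timing of one secondary parameter, which is not among the three that section 4.4 calls the main ones. It can be corrected because the pump switch is observable.

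Carry-over of acid into the primary recording is a plausible risk of unknown size and direction. Two stronger readings are tempting but unsupported. One is that less sensitive patients carry a stated multiple of the acid load of others; any such multiple needs an assumed time to pain that the protocol does not give, and it would describe acid infused rather than acid remaining. The other is that a single spurious period turns a patient positive; section 4.4 plans on proportions of patients with episodes, but no one-episode rule is stated.

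Overall this is a minor-to-moderate correction. No sample size or power figure changes.

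**What to change.** Reconcile sections 5.2.1 and 5.2.2:

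- Delete the pH < 1.0 marker. Define time zero as the recorded pump switch from saline to acid plus a fixed dead-space delay (measured dead volume ÷ 8 mL/min), identical for all subjects.
- State a fixed start for the analysed pH-impedance window that the equipment in place can observe, for example the start of the standardized meal. Alternatively, keep the full recording and add a sensitivity analysis that excludes the fasting half-hour. A rule tied to the return of pH to its pre-infusion level would not work in the written order, because no pre-infusion pH is recorded.
- Report infused acid volume by group, so that any imbalance is visible.

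The cost is a few sentences of rewording, one measurement of line dead volume, and at most 30 of 1440 minutes (2.1%) of recording lost from the pH-impedance analysis. A start at the meal limits carry-over but does not prove that the acid has cleared.
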